### Study setting

2.2

The RCT will be conducted in a hybrid setting combining routine clinical care in hospital-based pediatric endocrinology outpatient clinics with real-world daily environments. Baseline and post-intervention assessments will be performed during routine outpatient visits by healthcare professionals trained in standardized assessment procedures, and data will be recorded through the Diactive-1 clinical web-based platform. The 12-week duration is supported by preliminary Diactive-1 findings showing relevant effects within this timeframe (10, 24). The intervention will be delivered through the Diactive-1 mHealth app in participants’ daily environments, distinguishing it from usual clinical care.

The project was initially approved by the Medical Research Ethics Committee of Navarra (PS_2025/5), approved on March 25, 2025, and has undergone additional review by the ethics committees of each hospital. The study will adhere to the ethical guidelines of the Declaration of Helsinki, the Singapore Statement, and the Oviedo Convention on Human Rights and Biomedicine.

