### Randomization, allocation concealment, and blinding

2.5

The randomization sequence assigning participants to the study groups (i.e., exercise intervention group and usual care wait-list control group) will be generated by a computerized algorithm with no human access and implemented via the centralized Diactive-1 web-based platform. The algorithm will use a non-stratified randomization scheme with small, randomly varying even block sizes (i.e., 2, 4, 6, and 8 participants). Each block will contain an equal allocation ratio between the two groups (50%–50%), with the order of assignments within each block randomly permuted, thereby ensuring balance between groups throughout recruitment while minimizing predictability of the sequence. Because recruitment per hospital may vary, randomization will be centralized and non-stratified, with hospital-level clustering accounted for in the mixed-effects models. To ensure allocation concealment, randomization will be automatically performed after completion of the baseline clinical visit and entry of the corresponding clinical data, before the 7-day diabetes-related data-collection period.

Participants and healthcare professionals cannot be blinded due to the nature of the intervention. Outcome processing and statistical analyses will be performed using coded group allocation whenever feasible. The statistical analyst will remain blinded to group identity until the primary analyses have been completed. All hospitals and participants registered on the Diactive-1 web-based platform will be coded using alphanumeric identifiers.

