### The Diactive-1 web platform

2.6

The Diactive-1 web platform (version 1.0) is a secure software system developed to connect the participating pediatric endocrinology units with the project coordination team. The platform supports three user roles: healthcare professionals, participants, and the coordination team. Access will be role-based, password-protected, and restricted to the minimum information required for each user profile.

Upon initial access, healthcare professionals will be required to complete tutorial videos covering platform functionality, CGM and insulin pump data extraction, study protocol procedures, standardized handgrip dynamometry, and anthropometric assessment. Subsequent access will provide a hospital-restricted dashboard displaying participant-level data only for participants recruited at that hospital. Locally identifiable information required for clinical follow-up and participant management will be accessible only to authorized healthcare professionals at the recruiting site. Research data will be linked to a coded participant identifier.

A dedicated module will enable participant registration and data entry, including contact/access information, date of birth, biological sex, Tanner stage, anthropometry, disease-related clinical variables, insulin delivery modality, pump and CGM system information, and handgrip strength. Direct identifiers, such as name and email address, will be stored separately from coded research data and will not be routinely accessible to the coordination team unless strictly required for study management or participant safety.

Healthcare professionals will also be able to upload de-identified or pseudonymized PDF files related to diabetes management, including CGM and AID reports. Before upload, direct identifiers will be removed whenever possible. Once baseline data have been entered and verified, the platform will interface with the randomization module described in Section 2.5 and generate group-specific access instructions through the secure platform.

Upon first access, participants will be required to view tutorial videos relevant to their study procedures. Participants allocated to the intervention group will additionally receive instructions on using the Diactive-1 mHealth app, including breathing techniques during movement, movement patterns, core muscle activation, and correct exercise execution. Participants will only have access to their own study-related content.

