### Primary outcome

2.9

The primary outcome will be the change in age- and sex-standardized handgrip strength z-score from baseline to 12 weeks. Handgrip strength was selected as the primary outcome because it is a feasible, standardized, and clinically practical indicator of muscular fitness that can be assessed consistently across participating hospitals and showed a significant between-group improvement in the previous single-center Diactive-1 trial (10). The trial will assess whether participants allocated to the intervention group show greater improvement in handgrip strength z-score than those allocated to the usual care group. Handgrip strength will be measured with the Takei III Smedley Type 297 digital dynamometer (Takei Scientific Instruments, Niigata, Japan), following The Youth Fitness International Test (YFIT) (35). Each participant will perform two maximal trials alternately with each arm, and the best value for each hand will be recorded. The average of the best right- and left-hand values will be used as the absolute handgrip strength value. Handgrip strength will then be standardized using FitBack^©^ sex- and age-specific reference values to obtain z-scores (30). Absolute handgrip strength in kilograms will be reported as a secondary outcome. This approach is supported by preliminary Diactive-1 trial findings showing a significant between-group improvement in handgrip strength z-score at 12 weeks (23).

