### Data monitoring

2.14

Data and safety monitoring will be performed by the principal investigator and coordinating center throughout the trial. Monitoring will include remote review of recruitment and follow-up status, informed consent documentation, data completeness and consistency, adverse event records, app-recorded safety information, and adherence to intervention and assessment procedures. Deviations or data-quality issues will trigger documented corrective actions. The Diactive-1 web portal will provide a timestamped audit trail of relevant user actions, enabling remote verification of data integrity and site compliance. No formal data monitoring committee will be established, as the intervention is low-risk, non-pharmacological, and conducted alongside standard clinical care. Safety monitoring will remain independent of the funder, and any potential conflicts of interest will be disclosed in the “Funding” and “Conflicts of Interest” sections.

No interim efficacy analyses or formal stopping rules have been planned. However, if safety concerns, recurrent serious adverse events, or protocol-related risks are identified, the principal investigator may recommend temporary suspension, protocol amendment, or early termination of the trial. Any such decision will be documented and reported to the relevant ethics committee and institutional bodies in accordance with applicable regulations and local procedures.

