Major methodological strengths include the multicenter design, centralized computerized randomization with allocation concealment after baseline data entry, a comparator aligned with usual clinical care, and blinded outcome processing by the coordinating and statistical team. By bringing handgrip strength assessment into routine outpatient visits, the trial also explores the clinical feasibility of incorporating a functional marker of youth fitness into pediatric type 1 diabetes care, beyond traditional glycemic and cardiometabolic monitoring. The intervention is well specified through algorithmic progression based on handgrip-strength percentiles, prespecified training modalities, app-recorded exposure variables, glucose thresholds for session eligibility, and CGM- or AID-specific educational messages, which strengthens reproducibility and later interpretation of fidelity, adherence, and dose-response findings. The combination of clinical outcomes, glycemic technology, subjective barriers, physical literacy, quality of life, diet, and psychological outcomes broadens interpretability by linking effectiveness with mechanisms, user experience, and behavioral implementation. Embedding the study in routine pediatric endocrinology outpatient care and real-world daily environments should improve ecological validity, although this pragmatism also increases exposure to site-level heterogeneity and co-intervention variability. Importantly, the multicenter design will also provide information on the feasibility of implementing Diactive-1 across hospitals with different clinical workflows, which is essential for future scalability within public healthcare settings.

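### Week 12 handgrip is measured by staff the protocol calls unblindable, with no stated step to keep the tester unaware of the arm, and the Discussion's claim of a blinded coordinating team conflicts with that team's monitoring role

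*Protocol article*

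**What the plan says.** **Who measures.** Section 2.2 states: "Baseline and post-intervention assessments will be performed during routine outpatient visits by healthcare professionals trained in standardized assessment procedures". Section 2.6 requires these professionals to watch tutorials that include handgrip dynamometry. Section 2.5 states: "Participants and healthcare professionals cannot be blinded due to the nature of the intervention".

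**What is measured.** Section 2.9: "Each participant will perform two maximal trials alternately with each arm, and the best value for each hand will be recorded". The two best values are averaged and converted to an age- and sex-standardized z-score. Section 2.11 places the baseline grip test before randomization.

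**How allocation reaches the participant.** Randomization is automatic. The platform is then to "generate group-specific access instructions through the secure platform" (Section 2.6), and the app is activated for the intervention group only (Section 2.11).

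**What is said to be blinded.** Section 2.5 makes two statements: "Outcome processing and statistical analyses will be performed using coded group allocation whenever feasible" and "The statistical analyst will remain blinded to group identity until the primary analyses have been completed". The Discussion lists as a strength "blinded outcome processing by the coordinating and statistical team", without qualification.

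**What the coordinating side reviews.** Section 2.14 assigns monitoring to the principal investigator and the coordinating center. It covers "app-recorded safety information, and adherence to intervention and assessment procedures". Section 2.16 adds a weekly review of trial conduct by the coordinating team. Section 2.7 has the principal investigator ask an independent data manager for unblinding when it is needed.

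**The concern.** There are two separate issues.

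The first concerns the endpoint. A maximal grip reading depends on how hard the participant tries, and that can depend on how the tester encourages the attempt. Section 2.5 explains the lack of blinding by the nature of the intervention. That holds for participants and for clinicians who manage their diabetes. It does not hold for the person holding the dynamometer: the app delivers the training away from the clinic, allocation is automatic, and the platform issues the group instructions. A tester who knows the arm could, without intending to, encourage or record differently at Week 12. Such a difference would enter the primary contrast directly, most plausibly in favor of the app.

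The second concerns a stated property of the trial. If readers are told that the coordinating team processed outcomes blind, they will give the result credit for it. During follow-up, however, app safety and adherence records exist only for the intervention arm. Anyone who reviews them by coded participant can tell the arm.

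**Working it through.** **1. Is the tester kept unaware?** Three statements are read together:

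- Section 2.2: healthcare professionals perform the assessments.
- Section 2.5: healthcare professionals cannot be blinded.
- Section 2.9: the procedure is fixed (device, test battery, number of trials, scoring), but nothing is said about the tester's knowledge of the arm.

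Tester knowledge at Week 12 is therefore an inference from Sections 2.2 and 2.5 and is not stated outright. The Discussion's limitations name participants and clinicians as unblinded; the outcome assessor is not mentioned.

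**2. Where could a bias enter?** Section 2.15 estimates the effect as the between-group difference in change. If tester behavior adds b to the intervention arm's Week 12 mean, with complete data the estimate becomes

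(Week 12 + b − baseline) in the intervention arm − (Week 12 − baseline) in usual care = true effect + b.

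Baseline is measured before allocation, so it contributes nothing to b.

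**3. The plan's own figures.** Section 2.4 gives a difference of 0.24 z, d = 0.56, two-sided α = 0.05, 67 evaluable per group, 89.6% power and 15% attrition.

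- Noncentrality: 0.56 × √(67/2) = 3.24 on 132 degrees of freedom; noncentral t power = 89.57%. The stated 89.6% reproduces.
- Recruitment: 134 / 0.85 = 157.6, rounded up to 158. This reproduces.
- Implied SD: 0.24 / 0.56 = 0.429.
- Standard error: 0.429 × √(2/67) = 0.074.

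**4. Sensitivity to an assumed bias.** The document gives no size for b, so every row below is an assumption. With no true effect, the two-sided rejection rate is the noncentral t power evaluated at d = b / 0.429 with 67 per group.

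| Assumed b (z) | b / 0.24 | b / SE | Rejection rate (nominal 5%) |
|---|---|---|---|
| 0.02 | 8% | 0.27 | 5.8% |
| 0.05 | 21% | 0.68 | 10.3% |
| 0.10 | 42% | 1.35 | 26.8% |
| 0.12 | 50% | 1.62 | 36.3% |

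These rates hold for any differential shift, including extra effort by participants who know their arm. If the tester accounted for half of a total of 0.10, masking the tester would leave 0.05 and a rate of 10.3%, not 5%.

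**5. The blinding claim, place by place.**

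| Place | Content |
|---|---|
| Section 2.5 | Coded allocation where feasible; analyst blinded |
| Section 2.7 | Principal investigator must request unblinding, which presumes a blind |
| Section 2.11 | App activated in one arm only |
| Section 2.14 | Principal investigator and coordinating center review app safety records and adherence |
| Section 2.16 | Coordinating team reviews conduct weekly |
| Discussion | Coordinating and statistical team process outcomes blind |

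The Discussion claims more than Section 2.5. For the coordinating team the claim conflicts with Sections 2.14 and 2.16, and Section 2.7 does not fit the monitoring role that Section 2.14 gives the principal investigator.

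**The case against.** The lack of site-level blinding is disclosed in Section 2.5 and again among the limitations. The document never says who runs the dynamometer at Week 12, and staffing of a visit is a detail that an article may leave to the full protocol. Some site staff do need to know the arm: Section 2.12 has the clinical-research team review app-reported hypoglycemia and provides for interrupting sessions. The digital device, named test battery, fixed trials and required tutorials all limit the tester's discretion, and encouragement may already be scripted in material not shown here. Much of this stands. It shows that full masking is hard in routine clinics. It does not show that the tester must know the arm, and the one reason given for not blinding does not reach that person.

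On the second issue, the coordination interface in Section 2.6 does not list the arm among its fields, outcome processing may be done by people other than those who monitor, and averaging two values and applying reference tables leaves little room for judgment. This also stands, so the conflict lies in the claim made for the team as a whole. It is not evidence that processing will be biased.

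A reader might go further and infer that the statistical analysis is unblinded. The documents do not support that: nothing contradicts the stated blinding of the analyst. Nor do they support reading 10% or 27% as this trial's actual false-positive rate. Those figures follow from assumed biases that also include participant effort.

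**Conclusion.** The point holds in a limited form. An effort-dependent primary outcome is measured at Week 12 by members of a group declared unblindable. The reason given does not apply to the act of measurement, and no stated step keeps the tester unaware. Separately, the Discussion claims a blind for the coordinating team that Section 2.5 does not promise and that Sections 2.14 and 2.16 undercut.

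The direction of any tester bias is plausibly toward benefit, but its size is unknown. The table shows only that the planned effect of 0.24 z leaves little margin: a shift of about one fifth of it would double the nominal error rate. That rests on the implied SD of 0.429, 67 evaluable per group and a freely assumed b. No stated figure in the sample size section is affected by this point. It should be addressed because the remedy is cheap and the blinding statement needs correcting in any case.

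**What to change.** **At the Week 12 visit.**

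- Measure grip first, before any CGM or app review.
- Use the same scripted encouragement in both arms.
- Enter the value on a form that displays neither the arm nor the baseline grip. Hiding the baseline does not mask the arm, but it removes the number against which an improvement would be judged.
- Where possible, have the test done by existing staff who have not been told the allocation.
- Record whether the tester knew the arm and report this descriptively by group. Do not repeat the primary analysis by that flag: it arises after randomization and is probably related to arm and app engagement, so the subgroup contrasts could themselves be biased.

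**In the text.**

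- Limit the Discussion's blinding claim to the statistical analyst, or state that staff who review app data take no part in outcome processing.
- Reconcile the claim with Sections 2.5, 2.7, 2.14 and 2.16.
- Add unblinded outcome assessment to the limitations.

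**Cost.** A platform display setting, an order of procedures, a short script, one recorded item and some rewording, with no extra participants or staff. Masking will be incomplete where the treating clinician takes the measurement, and bias from participants' own effort will remain.

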### The Diactive-1 web platform

2.6

The Diactive-1 web platform (version 1.0) is a secure software system developed to connect the participating pediatric endocrinology units with the project coordination team. The platform supports three user roles: healthcare professionals, participants, and the coordination team. Access will be role-based, password-protected, and restricted to the minimum information required for each user profile.

Upon initial access, healthcare professionals will be required to complete tutorial videos covering platform functionality, CGM and insulin pump data extraction, study protocol procedures, standardized handgrip dynamometry, and anthropometric assessment. Subsequent access will provide a hospital-restricted dashboard displaying participant-level data only for participants recruited at that hospital. Locally identifiable information required for clinical follow-up and participant management will be accessible only to authorized healthcare professionals at the recruiting site. Research data will be linked to a coded participant identifier.

A dedicated module will enable participant registration and data entry, including contact/access information, date of birth, biological sex, Tanner stage, anthropometry, disease-related clinical variables, insulin delivery modality, pump and CGM system information, and handgrip strength. Direct identifiers, such as name and email address, will be stored separately from coded research data and will not be routinely accessible to the coordination team unless strictly required for study management or participant safety.

Healthcare professionals will also be able to upload de-identified or pseudonymized PDF files related to diabetes management, including CGM and AID reports. Before upload, direct identifiers will be removed whenever possible. Once baseline data have been entered and verified, the platform will interface with the randomization module described in Section 2.5 and generate group-specific access instructions through the secure platform.

Upon first access, participants will be required to view tutorial videos relevant to their study procedures. Participants allocated to the intervention group will additionally receive instructions on using the Diactive-1 mHealth app, including breathing techniques during movement, movement patterns, core muscle activation, and correct exercise execution. Participants will only have access to their own study-related content.

The coordination team interface will display a centralized list of coded participants, including creation date, affiliated hospital, questionnaire completion status, remaining study days, and follow-up status. The coordination team will not have routine access to direct participant identifiers. Any data correction after verification will require an authorized, documented, and audit-trailed amendment rather than unrestricted editing.

### Procedure for unblinding if needed

2.7

The coordination team may unblind the data when necessary to ensure participant safety, following a medical request or a formal request from the ethics committee. In such cases, the principal investigator will request unblinding through the independent data manager using the Diactive-1 system. Only strictly necessary information will be disclosed, and all cases will be thoroughly documented and reported to the relevant ethics committee.

### The Diactive-1 mHealth intervention

2.8

The central component of this 12-week RCT is the mobile application used by the intervention group during the study period. Diactive-1 is an mHealth application that delivers tailored resistance-training programs comprising more than 350 exercises and is intended to support, but not replace, exercise professionals. **Figure 1** presents the main app interface and user navigation screens. This line of research focuses on implementing innovative physical exercise-based educational strategies for individuals with chronic conditions, aiming to enhance self-management capacity through empowerment-oriented interventions, in accordance with guidelines from the International Society for Pediatric and Adolescent Diabetes (ISPAD) (29). By reducing uncertainty and facilitating real-time decision-making, Diactive-1 aims to support diabetes self-management. Diactive-1 should therefore be considered a multicomponent self-management package, and the trial will estimate the combined effect of its tailored resistance-training prescription, glucose-management education, safety thresholds, tutorials, and gamification rather than the isolated effect of resistance training.

